## Methods

This study aims to determine the extent to which a total of four wards in two psychiatric hospitals, where also involuntarily admitted patients are treated, can establish an open-door policy via additional staffing and strategic support. For this purpose, the same intervention is carried out in two psychiatric hospitals in Tuebingen and Friedrichshafen, where the two identical wards are either next to each other (Friedrichshafen), or on superimposed floors (Tuebingen). In both scenarios, one ward will serve as experimental, while the other will serve as control. The patients will be admitted in an alternating fashion. After one year, the ward which had previously been the control ward will receive the intervention. The intervention will be continued at the primary intervention ward. In the control wards, treatment as usual will take place. That is, ward doors will not stay closed throughout the first year but will be opened according to clinical considerations as has been previously practiced (so-called facultatively opened doors). After 12 months, the two control wards will undergo three months of implementation of the new policy and become intervention wards as well. Both hospitals provide similar conditions with identical ward architecture and an alternating patient admittance policy, so that the study can be carried out with the same study protocol and similar patient populations.

### Study design

The present study is a prospective controlled study with a quasi-experimental design.

### Ethics and consent

This study was approved by the ethics committee of Ulm University on March 1st, 2017, No. 313/16 and by the ethics committee of Tuebingen University on June 6th, 2017, No. 170/2017/BO1.

### Study participants

Data of all patients who are admitted to the acute wards of the University Department of Psychiatry and Psychotherapy Tuebingen and the Department for Psychiatry Friedrichshafen (part of the Clinic for Psychiatry and Psychotherapy I of Ulm University), between June 1st 2017 and March 31st 2020 will be collected. There is no specific target age group, but as only adults are treated at the participating wards, all patients will be over the age of 18. The 34 months of data collection include a four-month baseline phase, three months of implementation phase and a total of 27 months of intervention in the intervention wards. The investigation group is defined as those patients treated at the two intervention wards within the first 12-month period. The control group is defined as those patients treated at the other wards without specific interventions during the same period. To control for bias, we will compare distributions of diagnoses and how many patients are admitted involuntarily. In Tuebingen, we will also collect data on how long patients are allowed to leave the ward. In Friedrichshafen, there is no further differentiation, patients are either allowed to leave the ward or they are not. This represents different clinical practices which could not completely be harmonized. Furthermore, the number of patients and staff per day will be recorded.

### Recruitment of participants

Participants will not be actively recruited. All patients who are admitted to one of the two acute wards of the University Department of Psychiatry and Psychotherapy Tuebingen and the Department for Psychiatry Friedrichshafen during the 34-month period, will participate in the study without any exclusion criteria.

### Timeline and procedures

The planned timeline is shown in Fig. 1.

**Fig. 1 Fig1:**
[figure not shown]
Planned timeline

### Interventions

On each intervention ward, the open-door policy will be implemented as a mission expressed by the clinical director “to keep the door open by all reasonable efforts with high priority, but without running inappropriate risks”. That means it will still be possible to lock the door temporarily with good reasons (to be documented).

Staff will be fully informed about the project and introduced to the interventions (see below) before it starts. Patients will be informed about the open-door policy at admission. As a daily routine, independent of this project, patients come together with nurses to talk about upcoming events each morning. During this meeting, they will be informed about the current door status and questions can be clarified from day to day if necessary.

In detail, interventions will be:The door status will be discussed each morning with the complete staffing team (doctors and nurses) and specific reasons requiring a locked door will be identified.Weekly team meetings to discuss special events or concerns.Patients who are considered to be endangered or at risk, will be identified and the team obliged to discuss possible interventions, e.g. a more intensive care or specific arrangements for patients at risk. These could include accompanied leave, planned visits at home, activities on or outside the wards as well as therapeutic and deescalative talks.An additional nurse for the ward team will be deployed in Friedrichshafen beginning with the intervention period; in Tuebingen, nursing trainees will be involved in taking care of patients in need of support.An intervention known as the “Potsdam Table” has been implemented successfully several times [28]. This can be a small table with chairs, flowers, newspapers and a nurse as a contact person (professional, nurse) near the ward door. The purpose of this intervention is the establishment of a meeting facility that might dissuade endangered patients urging to leave the ward by deescalating conversations. Depending on the reasons why a patient wishes to leave the ward contrary to the agreement, the contact person can respond by offering contact, initiating activities, discussing the crisis and in case of doubt also deciding that the door should rather be closed.

As doors will only be opened after a careful risk assessment on a daily and situational basis, this approach does not require a termination condition. It will still be possible to close doors at any time when necessary (e.g. if a patient at risk wants to leave and other interventions do not work).

### Standard care

On control wards, the door will continue to be opened facultatively without additional interventions. This requires that all patients accept time agreements, and a sufficient number of staff is always present.

### Outcome measures

The primary outcome measures will be the average opening time of the four acute wards between 8 a.m. and 8 p.m. in percent, the percentage of treatment days with the door open (at least part time), as well as the number of involuntary treatment days with the door open. The latter means that if the door is open for one full day x and seven involuntary patients are present, this will count as 7 involuntary treatment days with open doors.

As secondary outcomes, the frequency of coercive measures (seclusion, restraint, involuntary medication), suicides, suicide attempts, severe self harm and aggressive incidents will be recorded as well as the frequency of absconding. This includes deviations from agreements in voluntarily treated patients, as well as searches for missing patients by the police. In Friedrichshafen, aggressive incidents will be documented with the Staff Observation Aggression Scale [29], in Tuebingen, the documentation of aggressive incidents is part of the survey which is to be filled out on a daily basis. Coercive measures will be routinely documented at both locations by a case register according to the law on assistance for persons with mental diseases in Baden-Wuerttemberg [2]. In addition, costs of the intervention per day with the door open are to be documented. Ward atmosphere will be assessed by staff and patients every six months by the Ward Atmosphere Scale [30].

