**Methods:**

This study investigates whether indicators of an open-door policy, as measured by a priori determined outcomes, can be improved by a defined complex intervention on two intervention wards in two psychiatric hospitals, compared to two control wards with otherwise very similar conditions. Both hospitals contain two wards identical in structure and patient admittance policies, so that a similar study protocol can be followed with similar patient populations. Both hospitals have a defined catchment area and receive voluntary and involuntary admissions. In a baseline phase, wards will be opened facultatively (i.e., if it seems possible to staff). In the following intervention period, one ward per hospital will establish an enhanced open-door policy by applying additional strategic and personnel support. As a control group, the control ward will continue to be opened facultatively. After one year, control wards will be opened according to the open-door policy as well. Interventions will include the continuous identification of patients at risk as well as the development of individual care concepts and additional staffing. For this purpose, nursing and medical staff will be methodically supported on an ongoing basis by study staff.

Outcomes variables will be the percentage of door opening on each ward between 8 a.m. and 8 p.m., the percentage of all treatment days with the door opened and the number of involuntary treatment days with open doors. Data on frequencies of aggressive incidents, absconding, police searches, and seclusion or restraint will be used as control variables. Additional costs will be calculated.

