### Sample size

The size of the sample is equivalent to the total of all patients admitted to the respective hospitals’ acute care units in the intervention period. As an estimate, we expect an amount of 560 admissions per year at each ward in Tuebingen and 420 at each ward in Friedrichshafen. With three months baseline and 24 months of intervention, we expect 4410 patients in 27 months in total.

With regard to the qualitative part of the study, we estimate a total of 280 participants. This includes five times two focus groups with patients and two focus groups with staff separately, with each seven participants for all the four wards, in total 280 patients and 56 professionals.

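### The third primary outcome is an unnormalised count, so it reflects the number of involuntary patient-days and the length of observation as well as door opening

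*Protocol article*

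**What the plan says.** Under Outcome measures, the protocol article names three primary outcomes. One is the mean daytime opening time of the wards, as a percentage. Another, also a percentage, is based on days: "the percentage of treatment days with the door open (at least part time". The remaining one concerns involuntary patients only and is an absolute figure: "the number of involuntary treatment days with the door open". The section shows how to form it with the example of a single day on which the door never closes: "seven involuntary patients are present, this will count as 7 involuntary treatment days with open doors". The abstract also calls it a number: "the number of involuntary treatment days with open doors". Neither place gives a denominator or a rate.

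Under Statistical analysis, linear or logistic models over time are planned, with no offset or exposure term named, and all analyses are called exploratory.

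Under Study participants, the investigation and control groups are defined over the same first 12-month period. The phases are "a four-month baseline phase, three months of implementation phase and a total of 27 months of intervention in the intervention wards". The same section says that the number of involuntary admissions will be compared as a check on bias, but does not connect that check to this outcome.

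**The concern.** This is the only primary outcome specific to involuntary patients, the group on whom the case for locked doors rests. The question is what part of their treatment can be given with the door open. A count answers a different question, namely how many such days occurred. That depends on how many involuntary patients were on the ward, for how long, and over what period.

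If the paired wards differ in involuntary days, the count mixes that difference with the effect on the door and can mask or exaggerate it. If phases of unequal length are compared, most of the apparent change can be calendar time. The authors intend to derive recommendations for guidelines from this study, so an outcome that cannot be read on its own matters even in an exploratory analysis.

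**Working it through.** **The plan's own figure.** Sample size expects 560 admissions per year on each Tuebingen ward and 420 on each Friedrichshafen ward. (2 × 560 + 2 × 420) × 27/12 = 1960 × 2.25 = 4410, as stated. No power calculation is given, so none can be checked.

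**Model.** From the counting rule: count = c × f × d, where c is the mean number of involuntary patients per day, f the share of days with the door open and d the number of days. The normalised version is (c × f × d)/(c × d) = f. The documents give no values for c or f; those below are assumptions for illustration.

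**Dependence on door opening.** With c = 5, moving f from 50% to 70% changes the daily contribution from 2.5 to 3.5, a ratio of 1.40. At fixed census and period the count is proportional to door opening.

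**Dependence on census, same period (d cancels).**

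| Ward A (c, f) | Ward B (c, f) | Count per day, A | Count per day, B | Count ratio B/A | Ratio of open shares |
|---|---|---|---|---|---|
| 5, 50% | 7, 50% | 2.5 | 3.5 | 1.40 | 1.00 |
| 7, 50% | 5, 70% | 3.5 | 3.5 | 1.00 | 1.40 |
| 7, 50% | 4, 70% | 3.5 | 2.8 | 0.80 | 1.40 |

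The first row shows a gain with no change at the door, the second hides a real gain, and the third reverses it.

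**How large an imbalance reverses the sign.** The count ratio is the census ratio times the door ratio, so the sign reverses only when the census ratio falls below 1/(door ratio). For 50% to 70% open the threshold is 1/1.4 = 0.71. For 50% to 80% it is 1/1.6 = 0.625. For 50% to 55% it is 1/1.1 = 0.91.

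**Size of chance imbalance.** Background and Discussion put the involuntary share at about 10%. Assume that it holds on these wards. Each arm has 560 + 420 = 980 admissions per year, hence about 98 involuntary. Treating these as Poisson, the 95% range for the relative difference between arms is 1.96 × √(98 + 98)/98 = ±0.28. At an assumed 20% share (196 per arm) it is 1.96 × √392/196 = ±0.20. At the edge of the ±28% range, the arms hold about 84 and 112, a ratio of 0.75. A true door ratio of 1.6 would then appear as 0.75 × 1.6 = 1.2, one of 1.4 as about 1.06, and one of 1.1 as about 0.83. These are admissions, not patient-days. Variation in length of stay would normally widen the range for days, but the documents give no figure for it.

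**Dependence on phase length.** With c and f constant, the total scales with months: 12/4 = 3.0 from baseline to the controlled period, and 27/4 = 6.75 to all intervention months. At c = 5, f = 50% and 30.44 days per month, the counts are 304, 913 and 2055, while the share is 50% each time. Sample size uses other lengths: "With three months baseline and 24 months of intervention, we expect 4410 patients in 27 months in total". With those, the factors are 12/3 = 4.0 and 24/3 = 8.0. The two statements of baseline length need to be reconciled.

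**The case against.** The other side has several good points.

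- The group comparison is concurrent. Both arms cover the same 12 months, so phase length cannot distort it. Each hospital supplies one ward to each arm, so the 560 versus 420 difference in admissions enters both arms equally. Both points stand.
- The paired wards are described as identical and filled by strict alternation, and involuntary admissions will be compared. This limits the imbalance. It does not settle the matter: alternation acts on total admissions, while the outcome counts days. Involuntary days also depend on length of stay, on later changes of legal status and on chance, and the planned check covers admissions only.
- Nothing in the article says that raw totals from phases of unequal length will be set against each other, and a model of daily values would remove the phase-length problem. That is fair. Daily values would still scale with the involuntary census.
- A count has its own use, as the volume of involuntary care actually given with the door open. That is a reason to report it, not to let it stand alone as a primary outcome.

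A reader might infer that the count follows census and time and not door opening, or that it is likely to give the wrong sign. The documents support neither. The count is proportional to door opening when the rest is fixed. A reversal with a substantial door effect, such as 6 against 12 involuntary patients per day at 80% and 50% open, needs a two-fold imbalance between alternately filled wards, well beyond the ±28% that chance gives for admissions. A reader might also suspect transfers of involuntary patients to the control ward. The article describes none in this trial; the redistribution reported in Background belongs to a cited Swiss study.

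**Conclusion.** The point holds in a limited form. As defined, the third primary outcome combines door opening with the number of involuntary days and the observation time, and neither the definition nor the analysis section separates them.

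In the controlled year, the error in the count ratio equals the ratio of involuntary days between the arms. Under the 10% assumption, chance in admissions alone could make a true ratio of 1.4 appear as about 1.06. The realistic harm is masking or exaggeration; reversal is plausible only with a small door effect or a large imbalance. Across phases the raw totals cannot be compared, with factors of 3 and 6.75 arising from time alone.

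The census and open-share values are illustrative, and the involuntary share on these wards is assumed. The structural conclusion depends on neither. The outcome should be fixed, but this is not a fatal flaw: the other two primary outcomes are already percentages and no confirmatory decision rests on this one.

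**What to change.** Define the outcome as involuntary patient-days with the door open divided by all involuntary patient-days, for each ward and phase. A count model with involuntary patient-days as offset would serve equally well. Report the raw count and the denominator by arm and phase, so that a reader can see whether a difference comes from the door or from the number of involuntary days, and whether the denominator itself moved under the policy. The same sentence should say how a partly open day counts, since the worked example covers only a fully open day. State one baseline length throughout.

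The cost is small: a changed definition and one more reported column, with no change to conduct. One point needs confirmation. Legal status is listed among the items recorded with door status (Data collection and management). Total patients per day are recorded (Study participants), and occupancy comes from in-house systems. Neither section says clearly that the daily number of involuntary patients is available for days with the door closed. The sponsor should confirm this, because the denominator depends on it.

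### Intervention cost per open-door day is an average cost; it understates the cost per open day gained, by an amount the article does not allow us to size

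*Protocol article*

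**What the plan says.** The cost item stands among the secondary outcomes in Outcome measures: "costs of the intervention per day with the door open are to be documented". The Methods paragraph of the abstract adds "Additional costs will be calculated", so the costs in view are those that the intervention adds to usual care.

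Three places show that doors are also open without the intervention:

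- Baseline (abstract, Methods): "In a baseline phase, wards will be opened facultatively (i.e., if it seems possible to staff".
- Control wards in the first year (Methods): "ward doors will not stay closed throughout the first year but will be opened according to clinical considerations".
- Standard care: "On control wards, the door will continue to be opened facultatively without additional interventions".

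Intervention wards are not open all the time either, because "it will still be possible to lock the door temporarily with good reasons" (Interventions).

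The cost sentence does not define an open day. The nearest definition belongs to one of the primary outcomes: "the percentage of treatment days with the door open (at least part time". The article gives no expected share of open time for any ward or phase, and no cost amount.

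**The concern.** The numerator is an increment: what the intervention costs on top of usual care. The denominator, as worded, is a total: days with the door open, with nothing subtracted for days that facultative opening would have produced anyway. An incremental cost over a total effect does not say what one more open day costs.

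The study asks whether extra staffing and support can establish an open-door policy, and it hopes to feed guideline recommendations. A reader deciding whether to fund the staffing needs the cost of the open time that it adds. The average figure makes each open day look cheaper than that. It also gives no signal when the intervention adds nothing, because the ratio remains an ordinary finite number.

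The design already supplies the missing comparison, in the form of a concurrent control ward in each hospital and a baseline phase.

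**Working it through.** **Inputs.** The article states no cost ratio and no open share, so there is no planned figure to reproduce. Let

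- C = additional cost of the intervention per ward-day (no amount given);
- p1 = share of days, or of time, open on the intervention ward (not given);
- p0 = the same share on the control ward (not given, but above zero in view of the Methods and Standard care sections).

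For simplicity the two wards are taken as equal at baseline, as the Randomization section suggests for their structure and case mix. All values of p0 and p1 below are assumptions.

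**Formulas.**

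- Planned measure: C/p1.
- Cost per open day gained: C/(p1 - p0).
- Ratio of the second to the first: p1/(p1 - p0). C cancels, so the factor depends on the shares alone. It exceeds 1 whenever 0 < p0 < p1.

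**Numbers.**

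| p0 | p1 | p1/(p1 - p0) |
|---|---|---|
| 0.1 | 0.9 | 0.9/0.8 = 1.125 |
| 0.2 | 0.8 | 0.8/0.6 = 1.33 |
| 0.3 | 0.8 | 0.8/0.5 = 1.60 |
| 0.4 | 0.8 | 0.8/0.4 = 2.00 |
| 0.5 | 0.8 | 0.8/0.3 = 2.67 |
| 0.6 | 0.8 | 0.8/0.2 = 4.00 |
| 0.7 | 0.8 | 0.8/0.1 = 8.00 |

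**When is the factor large?** It is at least k when p0 is at least p1(k - 1)/k. It reaches 2 only if p0 is at least half of p1, and 3 only if p0 is at least two thirds of p1.

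**Effect of the definition of an open day.** If a day counts as open when the door was open for any part of it, facultatively opened wards could score high. Assumed shares of 0.5 v 0.95 give 0.95/0.45 = 2.1, and 0.8 v 0.95 give 0.95/0.15 = 6.3. The cost sentence does not say that this definition applies.

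**No gain.** With p1 = p0 = 0.8 the planned measure is C/0.8 = 1.25C. The cost per open day gained is undefined, since p1 - p0 = 0.

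**The case against.** Four arguments deserve weight.

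1. *The figure is only descriptive.* The article says that it will be documented. It does not call it a cost-effectiveness ratio or a cost per open day gained, and it does not name the ward or period for the denominator. An average running cost per open day is a legitimate description. This stands, and is why the figure should be kept. It does not remove the mismatch, because the article chooses this unit itself and offers no other way of relating cost to opening.

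2. *The analysis plan may say more.* The abstract's separate statement on additional costs suggests costing against usual care. That concerns the numerator only. The point here is about a stated denominator, not about missing detail.

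3. *A null result would show elsewhere.* The primary outcomes measure opening on all four wards, so a reader could see that nothing was gained. This limits the harm, but a cost figure quoted alone would still mislead.

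4. *An incremental ratio has its own weaknesses.* It is unstable or undefined near zero gain. With one intervention and one control ward per hospital, no ward-level interval can be estimated within a hospital. Both are right, and the fix allows for them.

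A reader might also infer that the cost is understated several fold. The documents do not support that. They give neither share, and with low control opening the factor is only about 1.1 to 1.6. A several-fold gap requires a control share of at least half to two thirds of the intervention share, and nothing in the article establishes this.

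**Conclusion.** The point holds in limited form. The planned figure is an average cost per open day, and it lies below the cost per open day gained whenever the control ward is open for some of the time but less than the intervention ward. The direction follows from the article's own account of facultative opening, given that the denominator is all open days on the intervention ward, which is the natural reading though not spelled out.

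The size cannot be fixed from the documents; the assumed shares in the table span about 1.1 to 8. Severity is minor: this is one secondary item, the Statistical analysis section treats all analyses as exploratory, and no primary conclusion depends on it.

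**What to change.** Keep cost per open-door day, labelled as a descriptive average. Add one sentence to the cost outcome along these lines: for the first 12-month concurrent period, additional cost (intervention minus control ward, net of the same difference at baseline) will be divided by additional open-door time or days (intervention minus control ward, net of baseline), separately for each hospital.

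Details to settle with it:

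- State which definition of an open day, or which measure of open time, the cost figures use.
- Express both differences per ward-day, because the baseline is shorter than 12 months.
- Report by hospital, since the added staffing differs: one extra nurse in Friedrichshafen, trainees in Tuebingen.
- Show the cost difference and the opening difference separately beside any ratio.
- Report no ratio when the gain is near zero or negative.
- Claim no ward-level interval within a hospital, as there is one ward per arm.

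The change needs no new door or staffing data: under Data collection and management, door status is recorded daily and staffing per day is taken from nursing schedules. The price is a less favourable and possibly unstable ratio.
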